##### Part III: Clinical outcome measures

2.9.2.3.

1.New receipt of organ support within 14 days post operation (new receipt of RRT; new receipt of mechanical ventilation (non-invasive included); new receipt of vasoactive agents);2.New-onset organ failure within 14 days post operation;3.ICU free and alive days within 14 days post operation;4.Mortality to 14 days post operation.

### Monitored parameters and data collection

2.10.

A web-based electronic database (Unimed Scientific, Wuxi, China) is used for data collection and storage. All data are input by the designated coordinator. Training for data entry was arranged by the provider of the electronic database before study commencement. The data required to be collected during different phases are shown in Figure 1.

**Figure 1 F1:**
[figure not shown]
Schedule of enrolment, interventions, and assessments. BRS, bicarbonated Ringer's solution; ARS, acetated Ringer's solution; SBE, standard base excess; Lac, lactate; SCr, serum creatinine; Cys C, cystatin C; NGAL, neutrophil gelatinase-associated lipocalin; SID, strong ion difference; AKI, acute kidney injury; RRT, renal replacement therapy. *This figure is created by [name].

### Data management, sample size and statistical analysis

2.11.

The principal investigator will be responsible for data management, safety, privacy, and quality. The reporting and presentation of this trial will follow the CONSORT guidelines (29). Based on the principle of intention to treat (ITT), a full-analysis set (FAS) will be performed on the population with outcome reporting. FAS will be used for the analysis of baseline characteristics and main therapeutic interventions. The safety set (SS) will include all enrolled patients to assess the safety profile of the study intervention.

According to the previous study (30) and our unpublished data, the change of SBE during operation is approximately −2 mmol/L with a standard deviation of 2.5 mmol/L in patients receiving ARS. We estimated that a sample size of 72 participants (36 per group) could provide 80% power at a two-sided alpha level of 0.05 to detect ≥1.7 mmol/L increase in the primary endpoint results from the use of BRS with a potential loss of 5% recruitments.

Descriptive statistics will be used to assess any marked baseline differences in demographics or outcome measures between the two groups. Comparisons of binary outcomes will be expressed as relative risk with 95% confidence intervals and comparisons of continuous outcomes as mean differences together with 95% confidence intervals. Comparisons will be made using *t*-test and ANOVA for repeated-measures or Wilcoxon rank-signed test and Kruskall-Wallis according to the underlying distribution for continuous data and Chi-square or Fisher's exact *T* test for categorical data, as appropriate. Two-sided 5% significance levels will be used to identify statistically significant results. All confidence intervals reported will be 95% confidence intervals.

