### Randomisation

2.5.

The randomisation sequence will be generated by an independent statistician using SAS Version 9.4 with a fixed block size (block size = 4). Randomisation will be stratified by the surgical methods adopted (classical orthotopic liver transplantation vs. piggyback orthotopic liver transplantation). Allocation will be in a 1:1 ratio.

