#### Primary outcome measure

2.9.1.

The primary outcome measure is the change of SBE during the operation, reflected by the difference in SBE measure before and after the operation (ΔSBE = SBE_post_-SBE_pre_). SBE_pre_ will be measured before introduction of anaesthesia, and SBEpost will be measured shortly before transportation to the surgical ICU.

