As the infusion of sodium bicarbonate to correct metabolic acidosis could significantly increase the pH and SBE, we worked out a standardised protocol for the use of sodium bicarbonate. The amount of sodium bicarbonate used perioperatively would also be recorded. Moreover, it is known that, compared with the piggyback technique, the classical surgical procedure involves excision of the recipient inferior vena cava (IVC), which requires cross-clamping of the IVC above and below the liver, as well as the portal vein. This results in a marked reduction in venous return and consequent haemodynamic instability (36). Therefore, patients undergoing classical liver transplantations would inevitably suffer more severe metabolic acidosis. However, both surgical approaches are widely used in the study site at the discretion of the surgical teams. Therefore, we adopted stratified randomisation to compensate for the confounding effect caused by surgical methods.

This trial has several strengths and limitations. This is the first randomised controlled trial providing high-level evidence evaluating the effect of bicarbonated Ringer's solution in patients undergoing liver transplantation. And the data will be reviewed by an independent data safety monitoring board to ensure the participants' safety. However, As a phase II RCT, the study has a relatively small sample size recruited from one centre and not sufficiently powered to detect a difffference in patient-centered outcomes like incidence of AKI post operation.

The present trial is sponsored by Jinling Hospital of Nanjing University, which is the municipal centre for liver transplantation performing more than 120 liver transplantations annually. Thus the study is expected to be concluded within a year.

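### The tests named for the primary ΔSBE comparison carry no term for baseline SBE or for the surgical-method strata, so precision that the design already pays for may go unused

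*Protocol article*

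**What the plan says.** - **Primary outcome (section 2.9.1).** The outcome is the change in SBE over the operation, "reflected by the difference in SBE measure before and after the operation", that is ΔSBE = SBE_post − SBE_pre. SBE_pre is taken before anaesthesia starts and SBE_post shortly before transfer to the ICU.
- **Randomisation (section 2.5).** "Randomisation will be stratified by the surgical methods adopted": classical versus piggyback, 1:1, fixed blocks of four.
- **Reason for stratifying (Discussion, section 3).** The article expects classical transplantation to produce worse metabolic acidosis without exception and states that "we adopted stratified randomisation to compensate for the confounding effect caused by surgical methods". It gives no size for the difference.
- **Analysis (section 2.11).** Results are to be given as "comparisons of continuous outcomes as mean differences together with 95% confidence intervals". The tests listed for continuous data are the t-test, repeated-measures ANOVA and rank-based alternatives, chosen by distribution. No covariate or stratum term is named.
- **Sample size (section 2.11).** 36 per group "could provide 80% power at a two-sided alpha level of 0.05" for a difference of at least 1.7 mmol/L, "with a standard deviation of 2.5 mmol/L in patients receiving ARS", allowing for 5% loss. This is an unadjusted two-sample calculation on the SD of the change.

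**The concern.** There are two separate inefficiencies.

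**Strata.** Stratified blocks keep surgical method nearly equal between arms, so its variance largely drops out of the treatment difference. An unadjusted t-test still counts that variance in the standard error. If surgical method affects ΔSBE, as the article expects, the test rejects less often than 5% under the null and the 95% interval covers more than 95%.

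**Baseline.** A change score fixes the slope of SBE_post on SBE_pre at 1. When the true slope is not 1, ANCOVA estimates it and leaves a smaller residual variance. Repeated-measures ANOVA on the pre and post values does not help: with two time points, its arm-by-time test is the t-test on the change.

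At stake is the width of the primary interval in a 72-patient trial whose results are also meant to help power a later Phase III study.

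**Working it through.** **1. Reproduce the plan's figure.** Inputs from section 2.11: δ = 1.7, SD = 2.5, two-sided α = 0.05, power 80%, loss 5%.

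n per arm = 2(1.960 + 0.842)² × 2.5² / 1.7² = 33.9, so 34. Then 34 / 0.95 = 35.8, so 36 per arm and 72 in total. The stated number reproduces.

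With 34 evaluable per arm, the noncentral-t power of the unadjusted test is 78.9%. The 95% CI half-width is 1.997 × 2.5 × √(2/34) = 1.21 mmol/L.

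**2. Strata.** The gap g in mean ΔSBE between surgical methods and the 50:50 split are assumptions. The total SD is held at 2.5.

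- Share of variance due to strata: R² = 0.25 g² / 6.25, which is 4% for g = 1 and 16% for g = 2.
- With arms balanced within strata, the true standard error is about √(1 − R²) times the one the t-test uses. The effective critical value is therefore 1.997 / √(1 − R²): 2.04 for g = 1 and 2.18 for g = 2. The corresponding two-sided error rates on 66 df are 4.6% and 3.3%.
- Simulation with stratified blocks of four and 68 evaluable patients agrees: about 4.5% and 3.2% (4.5–4.7% and 3.2–3.4% across separate runs). With a stratum term the rate is about 5%.
- In the simulation, adding the stratum term raises power from 79.4% to 80.5% for g = 1, and from 81.4% to 85.9% for g = 2. The half-width falls from 1.21 to 1.18 and from 1.21 to 1.11 mmol/L.

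**3. Baseline.** Let ρ be the pre/post correlation and k the ratio of post to pre SD; both are assumptions. Holding the change-score SD at 2.5,

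residual variance / change-score variance = k²(1 − ρ²) / (1 + k² − 2ρk),

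which is (1 + ρ)/2 when k = 1. The slope of post on pre is ρk. Power is for 1.7 mmol/L at 34 per arm on 64 df.

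| k | ρ | slope | variance ratio | residual SD | power |
|---|---|---|---|---|---|
| 1.0 | 0.3 | 0.30 | 0.65 | 2.02 | 92.9% |
| 1.0 | 0.5 | 0.50 | 0.75 | 2.17 | 89.0% |
| 1.0 | 0.7 | 0.70 | 0.85 | 2.30 | 85.0% |
| 1.0 | 0.9 | 0.90 | 0.95 | 2.44 | 80.9% |
| 1.4 | 0.5 | 0.70 | 0.94 | 2.43 | 81.2% |
| 1.2 | 0.7 | 0.84 | 0.97 | 2.46 | 80.2% |
| 1.4 | 0.7 | 0.98 | 1.00 | 2.50 | 78.9% |

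With equal variances the half-width runs from 0.98 (ρ = 0.3) to 1.18 mmol/L (ρ = 0.9), against 1.21 unadjusted. The gain vanishes as the slope approaches 1.

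**The case against.** **The plan is valid and consistent as it stands.** Endpoint, SD, sample size and t-test match one another, the sample-size target of about 80% power is met without adjustment, and any miscalibration is towards caution. This stands. It makes the point a recommendation and not a correction of an invalid analysis.

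**The article is condensed and an SAP may add the terms.** The list of tests is generic, covers all outcomes and applies as appropriate. This stands in part: one can say that the article names no stratum or covariate term, not that the final analysis will lack one. But the article does name its methods, and all are unadjusted, so this is a stated choice and not only a detail left out.

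**The size of the gain is unknown.** This stands. No pre/post correlation, separate SDs, stratum gap or stratum split is given. A small stratum gap adds about one point of power, and an uneven split would shrink the share of variance explained.

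A reader might also infer stronger claims that the documents do not support:

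- *That baseline SBE is ignored.* It is used, by subtraction. Only regression adjustment is absent.
- *That stratification fails to deal with surgical method unless it is modelled.* Stratified blocks balance the factor between arms whatever test follows, so the article's statement about confounding is sound. Only the gain in precision goes uncredited.
- *That the change score over-corrects chance baseline imbalance.* That needs a slope below 1, which is not documented, and it is not a bias over repeated randomisation.
- *That omitting baseline regression makes the test conservative.* That applies to the strata only; omitting the baseline term costs power.

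**Conclusion.** The point holds as one of efficiency and calibration. The estimate is unbiased, false positives are not inflated, and 72 patients need not change.

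If the strata differ in ΔSBE, the unadjusted test does not deliver the nominal 5% level: about 4.5% at an assumed gap of 1 mmol/L and 3.2% at 2 mmol/L, with a 50:50 split. This is the firmer half, because the article itself expects surgical method to affect acidosis. The baseline half is less certain: power between about 79% (slope near 1) and 93% (ρ = 0.3, equal variances), against 78.9% unadjusted. A range confined to 85% and above would be too favourable, since it depends on equal variances and a correlation no higher than 0.7.

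The change is worth making because the factor and the baseline measurement are already part of the design, but no particular gain should be promised.

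**What to change.** Prespecify, before outcome data are examined, that the primary analysis is an ANCOVA of SBE_post (equivalently ΔSBE, which gives the same arm coefficient) on arm, SBE_pre and surgical-method stratum as entered at randomisation. Report the adjusted mean difference with its 95% CI, and keep the unadjusted t-test on ΔSBE as a sensitivity analysis.

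The cost is one sentence in section 2.11 and two model degrees of freedom (66 to 64 at 68 evaluable). No new data or patients are needed, and the sample-size statement can stay as it is.

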### Study design

2.2.

The present study is an investigator-initiated, single-centre, superiority, randomised controlled trial. This trial was registered at the Chinese Clinical Trials Registry (ChiCTR2100046889).

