### Study interventions

2.7.

The only difference between the two study groups exists in the choice of perioperative intravenous isotonic crystalloid: bicarbonated Ringer's solution (BRS group) vs. acetated Ringer's solution (ARS group). The compositions of each crystalloid solution are displayed in Supplementary Table S1.
•*Group 1: BRS group*
Patients will receive bicarbonate Ringer's solution for fluid therapy during and within 48 h post operation.•*Group 2: ARS group*
Patients will receive acetate Ringer's solution for fluid therapy during and within 48 h post operation.

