##### Part II: Renal function-related measures

2.9.2.2.

All the **baselines** mentioned below refer to data obtained within 24 h before operation.
1.Incidence of AKI within 48 h after operation. AKI is defined as current serum creatinine (SCr) increased 1.5 times baseline value OR with an increase greater than 26.5 µmol/L.2.Serum Scr, Cys C levels at 0, 24 and 48 h post operation;3.Serum NGAL levels at 0, 12, 24 and 48 h post operation;4.Arterial pH, SBE, HCO_3_^−^, Lac, Cl^−^ at 5 min post reperfusion of the donor liver, 0, 6, 12, 24 and 48 h post operation;5.Effective SID (eSID = [Na^+^] + [K^+^] + [Ca^2+^] + [Mg^2+^]-[Cl^−^]-[Lac^−^]) at 5 min post reperfusion of the donor liver, 0, 6, 12, 24 and 48 h post operation;6.Requirement of new RRT within 14 days post operation;7.RRT free and alive days to 14 days post operation.

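### The rank tests named for non-normal continuous data do not fit the design: a signed-rank test for two independent arms, and Kruskal-Wallis for serial samples from the same patients

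*Protocol article*

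**What the plan says.** Section 2.2 describes a "single-centre, superiority, randomised controlled trial". Section 2.5 adds "Allocation will be in a 1:1 ratio", and section 2.7 has two groups that differ only in the crystalloid given. The arms are independent, and nothing in the article matches or pairs patients across them.

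The primary outcome (section 2.9.1) is one number per patient: "the change of SBE during the operation, reflected by the difference in SBE measure before and after the operation".

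Many secondary outcomes are serial (sections 2.9.2.1 and 2.9.2.2). Examples are "Serum NGAL levels at 0, 12, 24 and 48 h post operation", and the arterial acid-base variables and effective SID "at 5 min post reperfusion of the donor liver, 0, 6, 12, 24 and 48 h post operation".

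For continuous data, section 2.11 names the t-test and then "ANOVA for repeated-measures or Wilcoxon rank-signed test and Kruskall-Wallis according to the underlying distribution for continuous data". The same paragraph reports continuous comparisons as mean differences with 95% confidence intervals. The article names no rank-sum (Mann-Whitney) test and no rank method for repeated measures.

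**The concern.** The sentence has the form A and B, or C and D, depending on the distribution. The natural reading is that C replaces A and D replaces B, so signed-rank replaces the t-test and Kruskal-Wallis replaces repeated-measures ANOVA. On that reading both substitutes belong to a different data structure from the one they would be applied to.

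An analyst who found the SBE change skewed and followed the text would have a test that cannot be applied to two unpaired arms without inventing pairs. An analyst with skewed serial NGAL or lactate values would have a test that treats repeated samples from one patient as if they came from different patients. At stake are the fallback for the primary comparison and the handling of most serial secondary outcomes when normality is doubted.

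**Working it through.** **1. The planned sample size.** Inputs from section 2.11: difference 1.7 mmol/L, SD 2.5 mmol/L, two-sided alpha 0.05, power 80%, loss 5%. For two independent means:

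n per arm = 2 × (1.96 + 0.842)² × 2.5² / 1.7² = 2 × 7.85 × 6.25 / 2.89 = 33.95, rounded up to 34.

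With 5% loss: 34 / 0.95 = 35.8, rounded up to 36 per arm, or 72 in total. This matches the plan exactly. (The t-distribution version gives 35, then 37 per arm, or 74 in total, a trivial difference.) The trial was therefore sized for an unpaired comparison, which agrees with the t-test and not with a signed-rank test.

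**2. Tests against data structure.**

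| Outcome | Values per patient | Comparison needed | Rank test named, in sentence order | Fit |
|---|---|---|---|---|
| SBE change (primary) | 1 | two independent arms | signed-rank | no: needs pairs |
| SCr, Cys C | 3 | arms over time | Kruskal-Wallis | no: needs independence |
| NGAL | 4 | arms over time | Kruskal-Wallis | no |
| pH, SBE, HCO3, lactate, Cl, effective SID | 6 | arms over time | Kruskal-Wallis | no |
| Serum acetic acid | 7 | arms over time | Kruskal-Wallis | no |

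**3. Signed-rank across arms.** It would need arbitrary pairing. In simulation (34 evaluable per arm, SD 2.5, 4,000 runs, no true effect) the type I error is 4.7%, so the error rate holds. The result, however, depends on the pairing. In one simulated data set, p ran from 0.00008 to 0.062 over 2,000 random pairings, while the rank-sum test gave a single p of 0.0098. With skewed data (exponential shape assumed) and a 1.7 mmol/L effect, power was 86% against 96% for rank-sum.

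**4. Kruskal-Wallis on serial data, an illustration of misuse.** Suppose all six values per patient were pooled and the arms compared. The within-patient correlation ρ is not in the documents, so a range of 0.2 to 0.8 is assumed. The variance of the arm contrast is inflated by about 1 + (6 − 1)ρ, so the type I error is roughly 2 × Φ(−1.96 / √(1 + 5ρ)):

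| ρ | 1 + 5ρ | 1.96 / √(1 + 5ρ) | Type I error, approximate | Type I error, simulated (1,500 runs) |
|---|---|---|---|---|
| 0 | 1.0 | 1.96 | 5% | 4.5% |
| 0.2 | 2.0 | 1.39 | 17% | 16% |
| 0.5 | 3.5 | 1.05 | 29% | 28% |
| 0.8 | 5.0 | 0.88 | 38% | 39% |

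If Kruskal-Wallis were instead used to compare time points within one arm, the error goes the other way: the type I error falls to 1.9%, 0% and 0% at ρ = 0.2, 0.5 and 0.8.

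**5. A use that is valid.** Kruskal-Wallis on two arms at a single time point is the rank-sum test. A numerical check gave p = 0.1003 by both.

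**The case against.** The strongest reply is that the sentence is loosely written rather than wrong in intent. It never says respectively, and it ends by leaving the choice to what is appropriate. Its test names are careless elsewhere: Kruskal-Wallis is misspelt and Fisher's test has acquired a stray T. The signed-rank name could easily be a slip for rank-sum, especially as the preceding sentence reports between-group mean differences. Kruskal-Wallis could be meant for one time point at a time. This stands as a limit on how the point is worded. It does not remove the point: even if the first name is a slip, the published text needs correcting, and the serial outcomes still have no rank method that respects repeated sampling.

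Several stronger readings are tempting, and the article does not support them:

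- *Any departure from normality makes the comparison invalid.* Kruskal-Wallis at one time point is valid, and arbitrary pairing holds the error rate near 5%, though with an arbitrary result.
- *The primary hypothesis would be tested within an arm.* At the planning values (mean −2, SD 2.5, 34 patients) a signed-rank test in the ARS arm alone rejects in about 99% of trials and says nothing about BRS versus ARS. But section 2.1 sets a between-arm objective, and no section plans a within-arm test.
- *The plan's serial analyses carry a 16% to 39% error rate.* No section says that time points will be pooled.
- *The primary test will be picked after seeing the data, or repeated-measures ANOVA will drop every patient with a missing sample.* How the distribution is judged and how missing samples are handled may be set out in an analysis plan that is not shown, and the second also depends on the software procedure used.

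**Conclusion.** The point holds in limited form. As written, the non-normal fallback in section 2.11 names one test for paired data where the arms are independent, and one for independent observations where the samples are repeated within patients. This rests on reading the sentence in order, which is the natural reading but not an explicit statement.

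The t-test on one SBE change per patient is sound, the total of 72 reproduces, and neither is affected. No error rate can be attributed to the plan itself. The 16% to 39% shows only what one possible misuse would cost, and it rests on an assumed correlation, 34 evaluable patients per arm and normal data with a random patient effect. The text should be corrected before analysis because it governs the fallback for the primary endpoint and most serial secondary outcomes.

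**What to change.** Reword the analysis paragraph in section 2.11:

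- For between-arm comparisons of a single value per patient, replace the signed-rank test with the Wilcoxon rank-sum (Mann-Whitney) test.
- For serial outcomes, replace Kruskal-Wallis with a method that respects within-patient correlation. One example is a mixed model with arm, time, arm-by-time, baseline and surgical stratum, with skewed markers such as NGAL transformed. The Friedman test would not serve, because it addresses only the time effect within an arm.
- State in advance one between-arm primary analysis of the SBE change that yields the mean difference and 95% confidence interval the plan reports. A linear model with baseline SBE and surgical stratum would do this and would use the stratification already in section 2.5. Keep the rank-sum test as a sensitivity analysis.

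The cost is the rewording of one paragraph. No extra data, patients or visits are needed, and the sample size does not change.

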## Discussion

3.

Metabolic acidosis is common perioperatively, potentially leading to decreased renal blood flow and reduced glomerular filtration rate (31). The use of balanced solutions can prevent hyperchloremic metabolic acidosis, thereby avoiding AKI in some patients. However, in patients suffering hemorrhagic shock or undergoing major surgery, where the liver metabolism is impaired, the organic anions in conventional balanced solutions might remain strong anions and thus fail to maintain acid-base status. BRS, a novel balanced crystalloid buffered with bicarbonate rather than organic anions, may perform better in maintaining acid-base status under such circumstances. Paul et al. demonstrated that compared with ARS, BRS significantly reduced large acetate surges in cardiac surgical patients (32). Animal experiments and small clinical studies also observed similar phenomenons (33–35), but the impact on renal function was not assessed.

In patients undergoing liver transplantation, liver metabolism, essential for all organic anion buffered balanced solutions to function properly, is suspended in the anhepatic phase and severely compromised during the early neohepatic phase. BRS, therefore, is likely to benefit these patients by better sustaining the acid-base status and thereby protecting their renal function. However, no clinical study has investigated that yet. This study will, for the first time, provide evidence on the relative effects of BRS vs. ARS on acid-base state and renal injury in patients undergoing liver transplantation.

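### For the secondary serial outcomes, repeated-measures ANOVA is the only listed method made for serial data; a mixed model would use every reading and give arm differences at named times

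*Protocol article*

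**What the plan says.** Section 2.11 covers all continuous outcomes in one sentence: the t-test and "ANOVA for repeated-measures or Wilcoxon rank-signed test and Kruskall-Wallis according to the underlying distribution for continuous data", to be used as appropriate. It does not tie a method to an outcome; the entry that fits a series of readings is "ANOVA for repeated-measures". The same paragraph says that results will be given with "comparisons of continuous outcomes as mean differences together with 95% confidence intervals".

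The serial outcomes are all secondary:

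- Section 2.9.2.2: pH, SBE, bicarbonate, lactate, chloride and effective SID "at 5 min post reperfusion of the donor liver, 0, 6, 12, 24 and 48 h post operation" (six readings).
- Section 2.9.2.2: "Serum NGAL levels at 0, 12, 24 and 48 h post operation" (four readings).
- Section 2.9.2.2: "Serum Scr, Cys C levels at 0, 24 and 48 h post operation" (three readings).
- Section 2.9.2.1: serum acetic acid before operation and at the same six times (seven readings).

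The primary outcome is not serial. Section 2.9.1 states: "The primary outcome measure is the change of SBE during the operation", taken as one post-operative value minus one pre-operative value.

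On mechanism, the Discussion (section 3) says that liver metabolism "is suspended in the anhepatic phase and severely compromised during the early neohepatic phase". Section 2.7 continues the allocated fluid for 48 h after the operation.

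**The concern.** Repeated-measures ANOVA is a stated choice. The rank alternatives do not replace it for a series: neither the signed-rank test nor Kruskal-Wallis models a comparison of two arms over time.

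The method fits these data poorly in three ways.

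1. The classical form needs a complete row, so one missed reading removes the patient from that outcome's analysis. The trial records mortality to day 14 (section 2.9.2.3), so some incomplete series can be foreseen.
2. The time and arm-by-time tests assume sphericity. This is a condition on the covariances, and it becomes less plausible when readings close together correlate more strongly than readings far apart. The acid-base, acetate and NGAL schedules have uneven gaps; creatinine and cystatin C at 0, 24 and 48 h do not.
3. The F tests answer whether the arms differ on average over time, or whether the profiles differ in shape. Neither is an arm difference at a given time, although the rationale points to the time around reperfusion.

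At stake is the secondary acid-base and kidney-marker evidence. The Background says that the results could be used to power a Phase III study, for which time-specific estimates from as many patients as possible are more useful than omnibus tests.

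**Working it through.** **The plan's own figure.** Section 2.11 gives a difference of 1.7 mmol/L, SD 2.5, 80% power, two-sided 5% and 5% loss. n per arm = 2 × (1.960 + 0.842)² × 2.5² / 1.7² = 2 × 7.849 × 6.25 / 2.89 = 33.9, so 34. Allowing for loss, 34 / 0.95 = 35.8, so 36 per arm and 72 in total. The stated size is reproduced, and nothing below changes it.

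**Complete rows.** Expected complete patients = 72 × (1 − q)^k, where k is the number of scheduled readings and q the share missing per reading. The article gives no q. The values below are assumptions, with missingness independent across readings.

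| Outcome | k | q = 1% | q = 2% | q = 5% | q = 10% |
|---|---|---|---|---|---|
| Acetate | 7 | 67 | 63 | 50 | 34 |
| Acid-base, effective SID | 6 | 68 | 64 | 53 | 38 |
| NGAL | 4 | 69 | 66 | 59 | 47 |
| Creatinine, cystatin C | 3 | 70 | 68 | 62 | 52 |

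For example, 72 × 0.95⁶ = 72 × 0.735 = 52.9.

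**Sphericity.** Assumptions: six acid-base times, the reperfusion reading 1 or 2 h before time 0, 36 patients per arm, and correlation r^(gap/12 h) with r from 0.3 to 0.9. The Greenhouse-Geisser epsilon falls from 0.74 to 0.44 as r rises (1 would be sphericity). With 4,000 simulated trials per setting and no true difference, rejection rates at a nominal 5% were:

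- arm-by-time test, uncorrected: 6.8% to 9.7%;
- arm-by-time test, Greenhouse-Geisser corrected: 4.5% to 5.0%;
- arm main effect: 4.2% to 5.5%, consistent with 5%.

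The simulation error is about √(0.05 × 0.95 / 4,000) = 0.3 percentage points. With equal correlations throughout, the uncorrected test rejected 5.2%.

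**Averaging over time.** Assumptions: SD 2.5 at each time, 36 per arm, no missing data, the reperfusion reading 1 h before time 0, and 12-h correlation r. The SD of a patient's six-reading mean is 2.5 × √(average entry of the correlation matrix). A comparison at 0 h alone with a difference of 1.7 has 81% power.

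| r | SD of mean | Power, fading effect | Power, persisting effect |
|---|---|---|---|
| 0.5 | 1.76 | 45% | 98% |
| 0.7 | 2.01 | 36% | 94% |
| 0.9 | 2.32 | 29% | 87% |

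The fading profile is 1.7, 1.7, 0.85, 0.4, 0, 0, with mean 4.65 / 6 = 0.78. The persisting profile is 1.7 at all six times. Averaging loses much power in the first case and gains some in the second.

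**The case against.** The strongest reply is that section 2.11 already promises mean differences with 95% confidence intervals and lists the t-test, so arm differences will be reported. A reader might infer that the plan yields no arm difference at the relevant times; the text does not support that. What stands is narrower: the ANOVA F tests are not the source of those differences, and the section does not say at which times they are taken.

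Second, nothing says that incomplete patients are dropped. That is the classical default of the method, and handling of missing readings may sit in an analysis plan that is not shown. The only loss figure given is 5% of recruits overall. At 1% to 2% missing per reading, 64 to 68 patients remain, a modest loss. The larger losses need higher rates that the article neither states nor excludes.

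Third, sphericity touches only the within-patient tests, and a standard correction repairs them. This is correct.

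Fourth, a reader might infer that a real early effect would be missed. That depends on the effect fading. Because section 2.7 continues the allocated fluid to 48 h, a persisting difference is also plausible, and the averaged test then has more power than a single time. For SBE itself, the end-of-surgery comparison is close to the primary outcome, which has its own test.

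These replies limit the size of the point. They do not show that the ANOVA is the better choice for these series.

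**Conclusion.** The point holds in a limited form and for secondary outcomes only. The method named for serial data uses less of the data than it could, has an arm-by-time test that is too liberal unless corrected, and does not directly produce the estimates that the same section promises.

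The loss of patients for the six-time outcomes ranges from 4 of 72 (1% missing per reading) to 34 of 72 (10%). The uncorrected arm-by-time test runs at about 7% to 10%. Both ranges rest on assumed missingness and correlations, since the article gives neither. The effect of averaging over time can go either way and does not by itself count against the plan.

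The primary analysis and the sample size of 72 are not in question. The change is worth making because it is inexpensive.

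**What to change.** In section 2.11, replace repeated-measures ANOVA with a likelihood-based linear mixed model using all observed readings. Include arm, time as a category, arm-by-time, the baseline value where one is collected, and the surgical-method stratum used in the randomisation (section 2.5). Use an unstructured covariance, with a simpler structure named in advance in case the model does not converge.

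Report the arm difference with 95% CI at each scheduled time. For the acid-base series, name 5 min after reperfusion and 0 h in advance as the key contrasts.

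The cost is a covariance fallback rule and slightly more analysis work. No new data or patients are needed. The model does not remove bias if missing readings depend on values that were never observed, so the number of readings available per arm and time should be shown beside the estimates.
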